#### 2.8.2. Secondary Outcome Variables

##### Home Injury Risk Assessment

Home injury risk will be assessed using a scale developed by the researcher, based on expert consultation and prior research [25,26,27,28,30,31,37,38,39]. The scale comprises 79 items categorized into five subscales: environmental risk assessment (37 items covering areas such as entrances, hallways, living rooms, bedrooms, and kitchens), fall injuries (12 items), cut and collision injuries (12 items), medication management (8 items), and swallowing disorders (10 items). Responses are scored on a binary scale (Yes = 1, No = 0), with higher total scores indicating a greater number of identified injury risk factors.

##### Home Injury Prevention Behaviors

Injury prevention behaviors at home will be assessed using a scale developed by the researcher, based on expert input and previous studies [25,26,27,28,30,31,32,38,40]. The 71-item scale is divided into six subscales: fall 13 items), cut and collision (7 items), burn and fire (24 items), medication management behaviors (7 items), swallowing disorder (9 items), and dehydration and heat-related illness prevention behaviors (9 items). Responses are scored on a binary scale (Yes = 1, No = 0), with higher total scores reflecting greater compliance with injury prevention behaviors.

The scale’s validity was confirmed by an expert panel comprising five professionals specializing in geriatrics, preventive medicine, geriatric nursing, emergency medical services, and occupational therapy. The item-content validity index (I-CVI) exceeded 0.80, and the scale-content validity index (S-CVI/Ave) was 0.90. The reliability of the scale, measured using Cronbach’s ⍺, was 0.87 in a pilot survey. The instruments were designed as self-administered questionnaires for community-dwelling older adults, and all assessors received standardized training prior to data collection to ensure consistency in administration and participant guidance.

##### Beliefs About Safety and Injury Prevention Behaviors

Beliefs about home safety and injury prevention behaviors will be measured using a scale developed by the researcher, based on the HBM [14,15,18] and previous studies [16,41,42]. The scale comprises five subscales: perceived susceptibility (four items), perceived severity (three items), perceived benefits (three items), perceived barriers (six items), and self-efficacy (four items). Each item will be rated on a 5-point Likert scale (1 = strongly disagree, 5 = strongly agree), with higher scores indicating stronger beliefs in preventive behaviors. The Cronbach’s ⍺ of this scale was 0.92 in a pilot survey.

##### Psychological Health

Depression

Depression will be assessed using the Korean version of the Geriatric Depression Scale-Short Form (GDS-SF) [43]. This 15-item scale utilizes a dichotomous response format, with “Yes” scored as 1 point and “No” as 0 points. Total scores range from 0 to 15, with higher scores indicating greater depressive symptomatology. Scores are categorized as follows: 0–5: no depression; 6–10: mild depression; 11–15: severe depression. In a previous study [43], the GDS-SF demonstrated a good internal consistency, with a Cronbach’s ⍺ of 0.88.

Fear of Falling

The fear of falling will be assessed using the Korean version of the Falls Efficacy Scale-International (FES-I) [44]. This 16-item scale utilizes a 4-point Likert scale (1 = Not at all concerned, 4 = Very concerned). Total scores range from 16 to 64, with higher scores indicating greater fear of falling. A score of 23 or higher is considered indicative of significant fear of falling [45]. A previous study [44] reported an excellent internal consistency for the FES-I, with a Cronbach’s ⍺ of 0.96.

##### Physiological Function

Muscle Strength: Grip Strength

Grip strength will be measured using a hand dynamometer (DongHwa Science Skill Takei, TKK-5401, Seoul, Republic of Korea). Participants will perform two trials with each hand. During each trial, they will hold the dynamometer with their arms lowered at their sides, angled outward at approximately 30 degrees, with the back of the hand facing outward, and exert maximum force. If testing both hands is not possible, the available measurement will be used. Higher dynamometer readings indicate greater grip strength. Grip strength is highly correlated with overall muscle strength, and it is widely regarded as a safe and reliable method for assessing strength in older adults [46].

Timed up and go test

To assess dynamic balance, the timed up and go test will be administered [47]. In this test, participants begin seated in a chair and, upon the tester’s signal, stand up, walk 3 m, turn around, walk back to the chair, and sit down again. The time taken to complete the sequence is recorded. A time of 30 s or more is generally considered indicative of an increased risk of falls and may suggest the need for assistance with activities such as walking, climbing stairs, or going outdoors. Participants will perform the timed up-and-go test three times, and the mean value will be used as the final result.

One-leg standing test

Static balance will be assessed using the one-leg standing test [48]. In the one-leg standing test, participants stand on a flat surface with their arms at their sides and their eyes open. They are instructed to select a comfortable leg to stand on while lifting the opposite foot off the ground. The time is measured from the moment they lift their foot until the lifted foot touches the floor. The longer of the two measurements is recorded as the final score. Higher scores indicate better static balance.

##### Health-Related Quality of Life

The health-related quality of life will be assessed using the Korean version of the 12-item Short Form Health Survey (SF-12) [49]. The SF-12 questionnaire comprises 12 items that evaluate physical and mental health across eight domains: physical functioning, physical role limitations, pain, general health perceptions, vitality, social functioning, emotional role limitations, and mental health. Each item is rated on a 3- or 5-point scale, with higher scores indicating better quality of life. In a previous study [50], the tool demonstrated an excellent internal consistency, with a Cronbach’s ⍺ of 0.91.

### 2.9. Data Analysis

Data analysis will be performed using SPSS version 26 (IBM Corp., Armonk, NY, USA). Descriptive statistics, including means, medians, frequencies, and percentages, will be used to analyze the general characteristics of the intervention and control groups. Normality of continuous variables will be assessed using the Shapiro–Wilk test. For normally distributed data, the homogeneity of participant characteristics and variables between groups prior to the intervention will be tested using the χ^2^ test, unpaired *t*-test, and one-way analysis of variance. Differences in score changes between the intervention and control groups at the three timepoints—baseline (T0), 1 week after intervention (T1), and 1 month after intervention (T2)—will be analyzed using repeated measures analysis of variance to evaluate between-group differences, within-group differences across the three timepoints, and interactions. For non-normally distributed data, analyses will be conducted using the Mann–Whitney U test and generalized estimating equations. All analyses will follow the intention-to-treat (ITT) principle, including all randomized participants in their originally assigned groups, regardless of adherence or withdrawal. Missing data will be handled using multiple imputation based on the fully conditional specification (FCS) method within SPSS version 26.0. Covariates such as age, sex, and baseline scores will be included to control for potential confounding factors.

To ensure robust statistical evaluation, Type I (alpha) error control will be prioritized, and the Holm–Bonferroni correction will be applied to maintain the overall significance level at *p* < 0.05 (two-tailed). An interim analysis will be descriptive only, focusing on data completeness and participant safety, without formal hypothesis testing to avoid Type I error inflation. Statistical significance will be set at a *p*-value of 0.05. Care will be taken to ensure that all participants complete the program and data collection, minimizing missing data through active follow-up.

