Beliefs about home safety among older adults are shaped by their perceptions and experiences, making targeted interventions essential for fostering a sense of safety. The health belief model (HBM) provides a theoretical framework for understanding injury prevention behaviors and supporting individual-level behavior changes [13]. HBM emphasizes the crucial role of the perceptions of health and injury risks, perceived benefits of preventive actions, and personal beliefs about safety among older adults, making HBM a valuable tool for inducing positive changes in preventive behaviors [14,15]. The validity of HBM as a theoretical framework has been demonstrated in previous studies on fall prevention interventions for older adults [16,17]. Program elements in this proposed study, such as video-based lectures and peer discussion sessions, aim to influence individual beliefs and indirectly foster positive changes in safety behaviors [14,18]. In addition, exercises and hands-on practice can serve as an effective educational method by allowing participants to directly experience, practice, and acquire specific coping skills, thereby enhancing their self-efficacy [19].

This study aimed to develop a protocol for the design of an HBM-based program to prevent unintentional home injuries in older adults. The program focuses on six key areas of home injury prevention and management: falls, cuts and collisions, burns and fires, swallowing disorders, medication management, and dehydration/heat-related illnesses. The program, termed “Safety and Home Injury Prevention Program for Seniors” (SHIPs), is designed to motivate older adults to adopt home safety and prevention behaviors, empower older adults to identify risk factors, and implement preventive actions, ultimately reducing injury occurrences. In addition, the program is designed to enhance psychological health, physical function, and quality of life, all of which may be adversely affected by injury incidents [20]. Furthermore, the protocol aimed to assess the feasibility of implementing the program before pursuing additional funding for a randomized controlled trial. The findings of this study are expected to provide practical guidelines for educators involved in injury prevention initiatives.

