### 1.1. Aims

#### 1.1.1. Primary Objectives

To evaluate the effectiveness of a Health Belief Model (HBM)-based health education program on the number of unintentional home injuries among community-dwelling older adults from baseline to post-intervention and at one-month follow-up.

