### 2.3. Sample Size

Sample size calculation was performed using G*Power 3.1.9.2. (Heinrich-Heine-University, Düsseldorf, Germany) Assuming a medium effect size of 0.25 [24], an alpha level of 0.05, a target statistical power of 0.80, an intraclass correlation coefficient of 0.5 to account for the correlation between repeated measures, two groups, and three measurement timepoints, the minimum required sample size was calculated to be 44 participants (22 per group). To accommodate a potential 20% dropout rate during the intervention period, the study aims to recruit a total of 54 participants, with 27 allocated to the intervention group and 27 to the control group.

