### 2.8. Outcomes Measures

#### 2.8.1. Primary Outcome Variables

The number of unintentional home injuries, including falls, cuts/collisions, burns/fires, medication-related incidents, swallowing disorders, and dehydration/heat-related illnesses, will be recorded. At baseline, the number of incidents occurring over the past 6 months will be assessed, whereas at 1 week and 1 month after the intervention, the number of incidents from the preceding month will be evaluated.

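### The 80% power is not derived for the primary outcome, an injury count, and section 2.9 does not fix one primary analysis for that count

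*Protocol article*

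**What the plan says.** Section 1.1.1 sets the primary objective as the effect of the programme "on the number of unintentional home injuries among community-dwelling older adults", and the hypothesis in section 1.2 concerns the same quantity. Section 2.8.1 defines it as a count over six injury categories: "The number of unintentional home injuries, including falls, cuts/collisions, burns/fires, medication-related incidents, swallowing disorders, and dehydration/heat-related illnesses, will be recorded". The recall periods differ: "At baseline, the number of incidents occurring over the past 6 months will be assessed", whereas at one week and one month after the programme "the number of incidents from the preceding month will be evaluated".

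Section 2.3 sizes the trial with "Assuming a medium effect size of 0.25", alpha 0.05, power 0.80, a correlation of 0.5, two groups and three timepoints. It arrives at 44 participants (22 per group), raised to 54 for 20% dropout. It gives no injury rate, rate ratio or dispersion.

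Section 2.9 has no analysis specific to the primary outcome. It states: "Normality of continuous variables will be assessed using the Shapiro–Wilk test". Repeated-measures ANOVA, with group, time and interaction effects, is the method for the three timepoints. The alternative is: "For non-normally distributed data, analyses will be conducted using the Mann–Whitney U test and generalized estimating equations". Age, sex and baseline values are to be covariates.

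**The concern.** The inputs in section 2.3 are those of an ANOVA on a continuous score. Power for a count depends on the event rate, the rate ratio, the exposure time and the dispersion, none of which appears. A reader would take 80% as the chance of detecting a worthwhile reduction in injuries, and nothing in the document supports that.

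The analysis is also not pinned down. The choice of method rests on a test applied to the trial's own data. Its non-normal branch names two methods without ranking them, and Mann–Whitney can use neither the planned covariates nor the repeated times. Neither branch says how a six-month count is to be set against one-month counts. The primary claim could therefore rest on any of several p-values.

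**Working it through.** **1. The plan's own figure.** Inputs from section 2.3: f = 0.25, alpha = 0.05, rho = 0.5, m = 3 timepoints, 2 groups. Noncentral F:

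- Interaction: lambda = f²·N·m/(1 − rho), df 2 and 2(N − 2). N = 26: lambda = 9.75, power 0.78. N = 28: lambda = 0.0625·28·3/0.5 = 10.5, power 0.81. N = 44: lambda = 16.5, power 0.956.
- Between groups: lambda = f²·N·m/(1 + (m − 1)·rho), df 1 and N − 2. N = 86: lambda = 0.0625·86·3/2 = 8.06, power 0.80. N = 44: lambda = 4.125, power 0.51.

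So the stated inputs give 28 or 86, not 44. N = 44 appears at a target of 0.95 for the interaction, or at 0.80 only with unstated inputs (non-sphericity epsilon 0.5, or rho = 0.2). The dropout step, 44/0.8 = 55 against 54, is close enough.

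**2. Power for the count.** The document gives no rate, so these are assumptions: control rate r = 0.1 to 1.0 per person-month, rate ratio 0.5, dispersion k = 0 (Poisson) or 1 (negative binomial), n = 22 per arm, two-sided 0.05. With mu0 = r·T and mu1 = 0.5·r·T over T months:

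SE = sqrt{[(1/mu0 + k) + (1/mu1 + k)]/n}; power = Φ(0.693/SE − 1.96).

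Example, r = 0.5, T = 2, k = 0: SE = sqrt[(1 + 2)/22] = 0.369; 0.693/0.369 − 1.96 = −0.08; power 47%.

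| r per month | T = 2, k = 0 | T = 2, k = 1 | T = 1, k = 0 | T = 1, k = 1 |
|---|---|---|---|---|
| 0.1 | 13% | 12% | 9% | 8% |
| 0.2 | 22% | 18% | 13% | 12% |
| 0.3 | 31% | 23% | 18% | 15% |
| 0.5 | 47% | 31% | 26% | 21% |
| 1.0 | 76% | 41% | 47% | 31% |

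This is a large-sample formula and is rough at the lowest rate, where 22 × 0.2 = 4.4 injuries are expected among controls over two months.

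**3. Why two months is an upper bound.** The first follow-up window ends one week after the programme. The second, ending one month after it, starts at about programme end. They share about a week, so distinct exposure is less than two months.

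**4. Where 80% is reached.** This needs SE ≤ 0.693/(1.96 + 0.842) = 0.247. With k = 0 and T = 2, SE² = 1.5/(22r), which gives r ≈ 1.1 per month. At r = 2.0 power is 96%. With all 27 per arm retained and r = 1.0, it is 84%. With k = 1 and n = 22, SE cannot fall below sqrt(2/22) = 0.302, so power stays below Φ(0.693/0.302 − 1.96), about 63%, at any rate.

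**5. Which branch a count takes.** In simulated trials with 22 per arm and control means of 0.1 to 2.0 per month (rate ratio 0.5 or 0.7, 400 runs per scenario), Shapiro–Wilk rejected normality in 96% to 100% of runs. The primary outcome would almost always go to the branch that the ANOVA calculation does not cover.

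**6. Unequal windows.** At a constant rate r the expected count is 6r at baseline and r at each follow-up: a six-fold drop with no effect. A chance group difference of d per month shows as 6d at baseline and d afterwards, which raw counts would present as a group-by-time interaction.

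**The case against.** Several points on the other side have force.

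- If a count is practically never normal, the branch is in effect known beforehand. That is right. A reader might infer that the trial's conclusion would swing between ANOVA and the alternative; section 5 of the check does not support that. What remains is the unranked pair within the non-normal branch.
- The normality test is stated for continuous variables, and a count is arguably not one. But then section 2.9 gives the primary outcome no clear route at all.
- Mann–Whitney may be meant for baseline comparisons and GEE for the repeated outcome. That is a natural pairing, but the sentence does not say so. It is not established that Mann–Whitney is the intended primary test.
- GEE and the covariates are already listed, and family, link and variance estimator may be left to an analysis plan. Agreed: their absence is not the fault. The fault is a data-driven rule and two unranked methods for the sole primary outcome.
- With six injury categories pooled, the rate may be higher than assumed. This stands, and it limits the power claim.

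A reader might also use the Background, where the protocol aims to "assess the feasibility of implementing the program before pursuing additional funding for a randomized controlled trial", to recast the comparison as estimation only. Sections 1.1.1 and 1.2 state an effectiveness objective and a superiority hypothesis, so that recasting is not supported.

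**Conclusion.** The point holds in this form. The stated 80% is unsupported for the injury count, and section 2.9 does not fix one primary analysis for it. Under the assumed rates, a halved rate and 22 per arm, power is at most about 13% to 76% (Poisson) or 12% to 41% (dispersion 1), and 8% to 47% on a single month. It is tempting to conclude that the trial cannot reach 80%. The documents do not support that: they give no rate, and Poisson power over two months passes 80% at about 1.1 injuries per person-month with 22 per arm. Separately, and without any assumed rate, 44 does not follow from the inputs printed in section 2.3, and no adjustment for the six-month and one-month windows is stated.

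**What to change.** **Section 2.9.** Name one primary analysis of the injury count, whatever Shapiro–Wilk shows: the GEE already listed, as a count model with log link, an offset for recall length, baseline rate, age and sex as covariates, and a small-sample robust variance. Report the group contrast at follow-up as a rate ratio with 95% CI. Say how an injury in the week shared by the two follow-up windows is counted. Restrict Mann–Whitney to baseline comparisons or secondary use.

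**Section 2.3.** State that the ANOVA calculation does not give the power for the injury count, and add a power range under stated rate, rate-ratio and dispersion assumptions. Correct the ANOVA figure: name the effect it refers to and give the matching number (28 for the interaction, 86 for the between-group effect), or disclose the further inputs that lead to 44.

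**Cost.** Wording in two sections and a less favourable stated power for the primary outcome. No extra participants are needed for these changes.

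### GEE is named for non-normal outcomes at 54 participants with no small-sample correction; the usual sandwich errors would put the covariate-adjusted group test at about 6–10% at assumed rates of 0.2–1 injuries per month

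*Protocol article*

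**What the plan says.** Section 2.9 (Data Analysis) sets the method by a normality check. Normal outcomes go to repeated measures ANOVA. For the others: "For non-normally distributed data, analyses will be conducted using the Mann–Whitney U test and generalized estimating equations". The software is SPSS 26. Age, sex and baseline scores are to be covariates, all randomized participants are analysed, and missing values are multiply imputed. On error control the section says: "To ensure robust statistical evaluation, Type I (alpha) error control will be prioritized, and the Holm–Bonferroni correction will be applied", with an overall two-sided level of 0.05.

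Section 2.3 (Sample Size) fixes the number of independent units: "the study aims to recruit a total of 54 participants, with 27 allocated to the intervention group and 27 to the control group". The stated minimum after dropout is 44, or 22 per arm.

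Section 2.8.1 makes the primary outcome the number of unintentional home injuries, counted over six months at baseline and over one month at each of the two follow-ups.

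For GEE the article names no variance estimator, link, working correlation or reference distribution. It neither adopts nor rules out a small-sample correction.

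**The concern.** GEE inference in its usual form takes standard errors from the sandwich variance and refers the test to a normal or chi-square distribution. Both steps are large-sample approximations in the number of independent units. With 22–27 people per arm the sandwich variance tends to be too small, and the reference distribution ignores that it is estimated. Covariates make this worse, because they use up part of an already small sample.

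The hypothesis in section 1.2 is a greater reduction in injuries across three timepoints. Of the two methods named for non-normal data, the Mann–Whitney test cannot fit a covariate-adjusted repeated-measures model, so the weight would fall on GEE. If its p-values are too small, the stated 5% is not held and the 95% intervals are too narrow. Holm–Bonferroni does not repair this, because it controls the family-wise error only if each p-value is valid.

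**Working it through.** **Inputs from the article.** Two arms of 27 (N = 54), or 22 (N = 44) at the planned minimum; two-sided level 0.05; covariates age, sex and baseline score; one-month counts at T1 and T2.

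**Inputs assumed.** Rates of 0.1–2 injuries per month, gamma-frailty dispersion of 0–2, complete data. The documents give none of these.

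**The plan's own figure.** The article states no level for GEE beyond the nominal 5%. Its only calculated figure is the sample size. The inputs there are f = 0.25 ("Assuming a medium effect size of 0.25"), power 0.80, ρ = 0.5 ("an intraclass correlation coefficient of 0.5 to account for the correlation between repeated measures"), and m = 3 occasions in two arms. For the interaction, λ = f²·N·m/(1−ρ) on 2 and 2(N−2) df, which first reaches power 0.80 at N = 28 (λ = 0.0625 × 28 × 3/0.5 = 10.5). For the between-group effect, λ = f²·N·m/(1+(m−1)ρ) on 1 and N−2 df, which needs N = 86 (λ = 0.0625 × 86 × 3/2 = 8.06). Neither gives 44. That is a separate matter; here 54 and 44 enter only as numbers of independent units.

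**Step 1: analytic level, no injury rate needed.** For approximately normal estimates without covariates, the uncorrected sandwich divides each arm's squared residuals by n instead of n−1.
- 1 df: level = P(|t on N−2 df| > 1.960·√((n−1)/n)). N = 54: 1.960·√(26/27) = 1.923, level **6.0%**. N = 44: 1.960·√(21/22) = 1.915, level **6.2%**.
- 2 df: level = P(F on 2 and N−3 df > 5.991·((n−1)/n)·(N−3)/(2(N−2))). N = 54: 5.991 × 26/27 × 51/104 = 2.829, level **6.8%**. N = 44: 5.991 × 21/22 × 41/84 = 2.791, level **7.3%**.

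**Step 2: simulated counts with the planned covariates.** No true effect, log-link GEE on T1 and T2, independence working correlation, adjusted for age, sex and baseline count, 3,000 trials per setting (Monte Carlo SE about 0.4–0.5 points). The table gives rejection rates for the 1-df group effect; both columns per N use the normal reference.

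| Rate per month | Dispersion | N = 54 uncorrected | N = 54 Mancl–DeRouen | N = 44 uncorrected | N = 44 Mancl–DeRouen |
|---|---|---|---|---|---|
| 0.2 | 1 | 7.0% | 3.8% | 7.8% | 3.6% |
| 0.5 | about 0 | 7.2% | 4.8% | 6.9% | 4.0% |
| 0.5 | 1 | 8.0% | 4.4% | 10.0% | 4.6% |
| 1 | 0.5 | 7.5% | 4.4% | 8.3% | 4.0% |
| 1 | 1 | 7.2% | 4.0% | 8.6% | 4.4% |

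A second simulation of this group effect, reaching down to 0.1 per month, gave 5.3–10.0% uncorrected at N = 54 and 5.1–10.1% at N = 44, against 1.7–5.2% with Mancl–DeRouen at N = 54. Together these support about 6–10% at 0.2–1 per month and near nominal at 0.1.

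For the 2-df group-by-time test over three timepoints at N = 54, adjusted for age and sex, the uncorrected level was 5.0–7.9%. Mancl–DeRouen with the chi-square reference gave 3.9–6.5%, so an F reference is useful there.

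**Step 3: no covariates, N = 54, 20,000 trials per setting, uncorrected.**

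| Rate per month | 1-df tests | 2-df interaction |
|---|---|---|
| 0.5–2 | 5.2–8.2% | 5.8–9.9% |
| 0.3 | 4.3–7.4% | 4.8–7.9% |
| 0.2 | 2.8–5.8% | 3.3–6.3% |
| 0.1 | 0.3–2.9% | 0.9–3.0% |

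At 0.1 per month, 25–29% of trials have an arm-by-time cell with no injuries. There the test is conservative or hard to estimate.

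**Step 4: a small Holm step.** With ten outcomes assumed, the first step is 0.05/10 = 0.005. In a model without covariates and with a log-exposure offset (which the article does not mention), the uncorrected 2-df test rejected in 0.51%, 1.16% and 1.04% of null trials at 0.3, 0.5 and 1.0 per month. It is therefore about exact at the lowest of these rates and about twice nominal at the other two.

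**The case against.** The strongest reply is that the article never says the uncorrected sandwich will be used. It says only GEE, and the choice of variance estimator is commonly left to an analysis plan that is not shown. That stands. A reader might infer that the plan chose an invalid estimator; the text does not support this, and every figure here is conditional on the usual form being used.

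Three further limits also stand.
- A reader might take it as settled that the injury count goes to GEE. Section 2.9 words its normality check for continuous variables and names two methods for non-normal data. The inference is very likely, since a one-month count at this size will hardly look normal, but it remains an inference.
- A reader might conclude that the p-values are certain to be too favourable. Without covariates and at sparse rates the error can run the other way, and the documents give no rate with which to choose between these cases.
- SAS is cited in section 2.5 only for the randomization sequence, while the analysis is fixed in SPSS 26. A change of software, and the pooling of corrected variances over imputed datasets, is more than a line of code.

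The reply does not remove the point. The article fixes the method family, the covariates and the number of participants, and promises priority for type I error control. In its usual form GEE would usually not keep that promise with those covariates, and a better form of inference is available.

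**Conclusion.** The point holds conditionally and is modest in size. If GEE is run with the usual sandwich variance and large-sample reference, the covariate-adjusted group test has a true level of about 6–10% in place of 5% at assumed rates of 0.2–1 injuries per month, and near 5% at 0.1. Equivalently, a nominal 95% interval would cover about 90–94% under no effect. The result rests on gamma-frailty counts, complete data, an independence working correlation and injury rates that the documents do not give. It does not touch the Mann–Whitney test. It is a recommended improvement to a method the article names only in outline, and does not show that the article states something false.

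**What to change.** State that all GEE analyses will use a small-sample bias-corrected sandwich variance (Kauermann–Carroll or Mancl–DeRouen), optionally with a t or F reference, and that effects will be reported with the corrected 95% confidence interval. Name software that supports this, which need not be SPSS 26, and say how the corrected variances will be combined across imputed datasets.

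The cost is slightly wider intervals, some work on software and pooling, and a conservative test at low event rates (about 2–4% at a nominal 5%). The change should be fixed before any unblinded analysis.
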